### Study objectives

No large-scale study has compared left unilateral versus bilateral sequential TBS for treating symptoms of MDD. The primary aim of this naturalistic, randomized double-blinded non-inferiority trial is to investigate the efficacy of unilateral (i.e., iTBS to the left DLPFC) and bilateral sequential (i.e., cTBS to the right DLPFC combined with iTBS to the left DLPFC) on reducing clinical symptoms of MDD. Based on previous research, we hypothesize that both treatments will effectively decrease depressive symptoms to a comparable degree (i.e., non-inferior) [33, 34, 61]. The incorporation of covariates during analysis may reveal a superiority of bilateral sequential TBS over unilateral treatment in specific subgroups. These subgroups include older individuals (≥ 60 years-old; [62], and/or individuals presenting with comorbid anxiety, and post-traumatic stress disorder [33, 63]). As mentioned, the clinical efficacy of rTMS is time limited [57, 58]. Therefore, this study will also investigate the efficacy of a six-month flexible maintenance phase. Additionally, to better understand the TBS-induced neurophysiological changes and their associations with therapeutic responses, multiple objectively measured neurophysiological variables will be assessed in this study. See Table 1 for a brief description of outcome measures and detailed hypotheses of this study. Ultimately, this study aims to: 1) inform whether unilateral TBS performed over the DLPFC is non-inferior to bilateral sequential TBS on treating MDD, 2) provide insight on neurophysiological mechanisms associated with treatment-induced effects and their longitudinal changes resulting from treatment, thus providing biomarkers of treatment response, and 3) explore neurophysiological markers, demographics, and clinical characteristics that may help identify responders and non-responders to treatment, paving the way for a more refined and personalized approach to TBS treatment.

**Table 1 Tab1:** Outcomes and hypotheses of the study

Outcome	Rationale	Hypothesis
Clinical (primary)	Investigate changes in severity of depressive symptoms	Unilateral TBS will be non-inferior in comparison to bilateral sequential TBS on reducing depressive symptoms

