## Data analysis

All statistical tests will be two-tailed, and significance (*p*-value) will be set at α = 0.05. All analyses will be performed on SPSS (Chicago, US) and/or using the open-source R statistical software (R core Team, Vienna, Austria and the R-Studio package rstatix; Kassambara, 2022). All data will be reported descriptively to summarize population characteristics. Unless otherwise stated, continuous data will be reported as mean and standard deviation (mean ± SD) and dichotomous variables will be reported as frequency (i.e., percentage) values.

All participants will be included in the analyses ‘as-randomized’ (i.e., bilateral and unilateral TBS) and data will be analyzed regardless treatment adherence and drop-outs. To this end, missing values in the data set (due to participants missing appointments, drop-out/discharge), if present, will be appropriately managed during analysis as per previous suggested procedures for clinical research [103, 104].

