### Sample size

Based on our power calculations and the findings from exemplary studies, our sample size offers sufficient statistical power for the planned statistical tests. For example, Plewnia et al. (2014), in *n* = 32 (16/group), found clinically meaningful differences in response to treatment rate (≥ 50% reduction in baseline MADRS score) when comparing 6 weeks of bilateral sequential vs sham TBS (56% vs 25%, respectively) [42]. In *n* = 60 (15/group), Li et al. (2014) showed that 2 weeks of bilateral sequential TBS had superior effectiveness in treating depressive symptoms (≥ 50% reduction in baseline HRSD-17 score) when compared to unilateral (iTBS or cTBS) or sham TBS [106]. For our primary (non-inferiority) statistical analysis (i.e., analysis of covariance, ANCOVA), a total sample size of *n* = 158 was calculated [Gpower Software V.3.1 [107]; power 0.80, α = 0.05, expected effect size *Cohen’s f* = 0.25 (medium; Cohen, 1988)]. For our analysis of predictors of response (i.e., regression analysis), a total sample size of *n* = 30–39 will be required for a regression model that includes 3–6 independent (and/or controlling) variables predicting 30% (R^2^) of variance in the outcome (dependent) variable (Gpower Software V.3.1 [107]; power 0.80, α = 0.05, expected effect size *Cohen’s f*^*2*^ = 0.43) [108]. All other statistical tests are exploratory and, therefore, no sample size calculations were performed. Therefore, in order to achieve the calculated sample size (*n* = 158), we aim to recruit a minimum of 171 individuals, considering an anticipated dropout rate of 6–8% based on previous research [37]. Our recruitment efforts will be capped at a maximum of 256 participants, aligning with our capacity to provide TBS treatment over a five-year timeframe.

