### Non-inferiority analysis – unilateral vs bilateral sequential TBS

As per Blumberger, et al. (2018), a non-inferiority analysis will be performed to investigate whether the proposed bilateral sequential TBS is non-inferior to the current FDA-approved unilateral iTBS [37]. An ANCOVA will be performed with the baseline HRSD-17 as controlling (i.e., covariate) and the final HRSD-17 score as the dependent outcome variable. The null hypothesis is that the baseline-adjusted final HRSD-17 scores for unilateral and bilateral stimulation will be comparable (i.e., non-inferior) [33, 34, 61]. Although, the incorporation of covariates (i.e., older individuals and individuals presenting with comorbid anxiety and/or post-traumatic stress disorder) during analysis may reveal a superiority of bilateral sequential TBS over unilateral treatment. During ANCOVA, potential missing data will be addressed using multiple imputation methods [104].

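### The non-inferiority hypothesis is stated backwards: the primary ANCOVA takes comparability as its null, so a non-significant difference could be read as non-inferiority

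*Protocol article*

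**What the plan says.** The section on the non-inferiority analysis gives the aim as follows: "a non-inferiority analysis will be performed to investigate whether the proposed bilateral sequential TBS is non-inferior to the current FDA-approved unilateral iTBS". The model is a two-arm ANCOVA: "An ANCOVA will be performed with the baseline HRSD-17 as controlling (i.e., covariate) and the final HRSD-17 score as the dependent outcome variable". The next sentence sets the hypothesis: "The null hypothesis is that the baseline-adjusted final HRSD-17 scores for unilateral and bilateral stimulation will be comparable (i.e., non-inferior".

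Study objectives uses the same proposition, with the same three citations, as the research hypothesis: "we hypothesize that both treatments will effectively decrease depressive symptoms to a comparable degree (i.e., non-inferior". Table 1 likewise lists non-inferiority in its hypothesis column for the primary clinical outcome.

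The Sample size section sizes this ANCOVA with "power 0.80, α = 0.05" and an expected Cohen's f of 0.25. It gives 158 participants for analysis and a recruitment cap of 256.

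The direction of the comparison also varies. The abstract and the non-inferiority section test bilateral against unilateral. The first numbered aim in Study objectives, and Table 1, test unilateral against bilateral.

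**The concern.** A test can reject its null or fail to reject it, but it cannot confirm it. In a non-inferiority trial, inferiority by at least a margin is therefore the null, and the type I error is a false claim of non-inferiority. Once comparability becomes the null, that protection is lost. The type I error is now the rejection of comparability when the arms are equal, and the false claim of non-inferiority becomes a type II error, which depends on the sample size and the noise.

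The sample size fits this reversed set-up. It starts from an effect expected to be detected, as for a test of difference, and not from a margin to be excluded.

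What is at stake is the headline conclusion. If a non-significant difference were taken as non-inferiority, a smaller or noisier trial would reach that conclusion more often, whatever the truth.

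**Working it through.** **1. The two statements side by side.**
- Study objectives and Table 1: non-inferiority is the hypothesis to be supported.
- Non-inferiority analysis: the same statement is the null.

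One proposition cannot be both in the same test. For a non-inferiority analysis the first role is the right one.

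**2. The plan's own sample size.** Inputs from Sample size: f = 0.25, α = 0.05, power 0.80. Method: non-central F with λ = f²N and denominator df = N − groups − covariates.
- 1 numerator df, which is what two arms have: N = 128.
- 2 numerator df: N = 158, the stated figure.
- Power at N = 158 with 1 numerator df: 88%.

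So 158 does not come from a two-arm comparison with these inputs. The error is on the generous side and is a separate matter. What matters here is that the calculation is for detecting a difference.

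**3. Chance of a non-significant result when the test arm is truly worse.** Inputs: two equal arms (1:1 allocation), one covariate, two-sided α = 0.05. N = 158 (planned for analysis) and N = 256 (the recruitment cap, taken as if all were analysed). The true deficit d is in units of the adjusted residual SD. The article gives neither SD nor margin, so the deficits are assumptions.

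Non-centrality = d√N / 2, df = N − 3. The probability is that of |t| below its critical value.

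| N | critical t | d | non-centrality | P(non-significant) |
|---|---|---|---|---|
| 158 | 1.975 | 0.30 | 0.30 × 12.570 / 2 = 1.885 | 53% |
| 158 | 1.975 | 0.45 | 2.828 | 20% |
| 158 | 1.975 | 0.50 | 3.142 | 12% |
| 256 | 1.969 | 0.30 | 0.30 × 16 / 2 = 2.400 | 33% |
| 256 | 1.969 | 0.45 | 3.600 | 5% |
| 256 | 1.969 | 0.50 | 4.000 | 2% |

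**4. The comparator.** A correct test declares non-inferiority when the upper limit of the two-sided 95% CI is below the margin. If the true deficit equals the margin, this happens 2.5% of the time at any N.

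**5. What a non-significant result leaves open.** The 95% half-width is (critical t) × 2/√N.
- N = 158: 1.975 × 2 / 12.570 = 0.314 SD. An estimate just short of significance has an upper limit near 2 × 0.314 = 0.63 SD.
- N = 256: 1.969 × 2 / 16 = 0.246 SD, with an upper limit near 0.49 SD.

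A non-significant result can therefore be compatible with a deficit of half an SD or more at N = 158.

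**The case against.** **The article never says that p > 0.05 means non-inferior.** This is correct. A reader might infer such a rule, but it is not written. The section models itself on a cited non-inferiority trial whose decision rule is not shown. The sentence may be a slip between null and research hypothesis, since it carries the same citations as the hypothesis in Study objectives. This limits the point to what the text permits. It does not make the sentence right: an analysis plan with a proper margin would have to contradict it.

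**The planned model can establish non-inferiority.** This is also correct. A reader might infer that no result of this ANCOVA could do so. But a result significantly favouring the test arm puts the whole interval on the favourable side of zero, which shows non-inferiority for any positive margin. The same model also yields the interval that the correct rule needs. The fault is in the hypothesis, not in the model.

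**Two-tailed testing is not a second fault.** The Data analysis section says "All statistical tests will be two-tailed". At 0.05 this fits a decision based on a two-sided 95% interval.

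**The as-randomised analysis is not a fault either.** The same section says "data will be analyzed regardless treatment adherence and drop-outs". A reader might infer that no per-protocol analysis will be run. The text does not say this is the only analysis set, and further sets are commonly left to the analysis plan.

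**The margin may be in a document not shown.** It may. Its absence from the article is not the finding, and a margin enters here only because the corrected hypothesis needs one.

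**Conclusion.** The concern holds in a bounded form. The null of the primary analysis is stated the wrong way round and contradicts Study objectives and Table 1. This is a wrong statement about the primary decision, not a detail left to another document, and it should be corrected before unblinding.

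The error rates in the working apply only if a non-significant difference is read as non-inferiority. They also rest on assumed deficits and on a residual SD set to 1, so they cannot be placed on the HRSD-17 scale from the article. The size depends strongly on N and on the deficit. It is serious at 158 for all three deficits and at 256 for 0.30 SD. At 256 it is about twice the nominal 2.5% for 0.45 SD (5.2%), and slightly below nominal for 0.50 SD (2.1%). The reversal itself depends on none of these figures.

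**What to change.** Replace the null-hypothesis sentence with:

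*H0: the baseline-adjusted mean difference in final HRSD-17 score (bilateral minus unilateral; higher is worse) is at least +M points. H1: the difference is below +M. Non-inferiority of bilateral TBS is concluded only if the upper limit of the two-sided 95% confidence interval from the ANCOVA is below M. A non-significant difference is not evidence of non-inferiority.*

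M must be a number of HRSD-17 points, justified and fixed before unblinding.

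Use one direction throughout. The text above follows the abstract and the non-inferiority section. Study objectives and Table 1 must be reconciled with it, or, if the reverse is meant, the arms in the rule exchanged.

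The change is to wording and the decision rule. It needs no new data and no new model. The cost is that non-inferiority becomes harder to claim. With a true difference of zero, 80% power and one-sided 0.025, the smallest margin that N supports is (1.960 + 0.842) × 2/√N. That is 0.45 adjusted SD at N = 158 and 0.35 at N = 256. For an assumed margin of 0.30 SD, power at N = 158 would be 47%. Once M and an SD are stated, the sample size should be checked against them.

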### Effectiveness of TBS treatment

Secondarily, the effectiveness of both unilateral and bilateral TBS as well as their difference on treating MDD will be investigated with generalized linear mixed models with treatment groups (unilateral vs bilateral TBS) as between-subjects factor, and outcome measures (clinical scores, neurophysiological measures) as within-subject factors. The main effects of Time (pre, post) and Time X Group (unilateral vs bilateral TBS) interaction will be investigated, and Bonferroni-adjusted pairwise comparisons will be performed to determine statistically significant within- and between-subjects differences. This analysis take into account missing data, avoiding the use of additional methods such as multiple imputations. The binominal outcomes will also be examined using Chi-Squared tests, and the difference in proportion rates between the groups will be reported (e.g., Groups: bilateral vs unilateral TBS, and outcome: % of response/remission rate identified as “yes” and “no” as per HRSD-17 ≤ 50% reduction from the baseline score [37, 43, 106]. If the sample size and their demographics allow for group stratification based on age groups, biological sex and gender, and the presence/absence of comorbidities, we will conduct additional between-subject analyses to compare groups.

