**CONMED**^g^	Current medication use [70]	Yes (type, dosage)/No	Baseline
**HRSD-17**^e,g^	Severity of depression [71]	Score range: 0–53 (0–7 no depression; 8–13, mild depression; 14–18 moderate depression; 19–22, severe depression; ≥ 23 very severe depression)	Baseline, end of week 2 and 4 (and final week of additional treatment for non-remitters^d^); beginning of maintenance weeks 1–13, 15, 17, 19, 21, and final visit (week 24)
**MADRS**^f,g^	Severity of depression [72]	Score range: 0–60 (0–6, absence of symptoms; 7–19, mild depression; 20–34, moderate depression; 35–60, severe depression)	Baseline, end of week 4 (and final week of additional treatment for non-remitters^d^); final visit (week 24)
**SRRS**^g^	Depression-related psychomotor impairments [73]	Score range: 0–60	Baseline, end of week 4 (and final week of additional treatment for non-remitters^d^); final visit (week 24)
**YMRS**^f,g^	Presence and severity of manic or hypomanic symptoms [74, 75]	Score range: 0–60 (2, euthymia; 3, depression; 12, mania)	Baseline, end of week 2 and 4 (and final week of additional treatment for non-remitters^d^); beginning of maintenance weeks 1–13, 15, 17, 19, 21, and final visit (week 24)
**C-SSRS**^a,g^	Quantify suicidal ideation and behaviour [76]	5 items rated yes or no, with additional clarifying questions	Baseline and end of weeks 1–4 (and both weeks of additional treatment for non-remitters^d^); beginning of maintenance weeks 1–13, 15, 17, 19, 21, and final visit (week 24)
**MMSE**^b,^^g^	Presence of dementia [77]	Score range: 0–30 (30–26, could be normal; 25–20, mild; 19–10, moderate; 9–0, severe)	Screening visit
**Physician consultation**^g^	Verify general suitability for TBS; clinical oversight	N/A	Before participants consent to the study, end of week 4 (or final week of additional treatment for non-remitters^d^), end of maintenance, and/or as needed throughout the study
**QIDS-SR**_**16**_^f^	Depressive symptoms [78]	Score range: 0–27 (0–5, no depression; 6–10, mild depression; 11–15 moderate depression; 16–20 severe depression; ≥ 21, very severe depression)	Baseline, end of weeks 1–4 (and both weeks of additional treatment for non-remitters^d^); beginning of maintenance weeks 1–13, 15, 17, 19, 21, and final visit (week 24)

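### The secondary mixed model compares change scores from two occasions only; adjusting for baseline and keeping the scheduled interim scores would give a more precise contrast, better protected against dropout

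*Protocol article*

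**What the plan says.** Under Effectiveness of TBS treatment, the protocol article specifies generalized linear mixed models with treatment group between subjects and "outcome measures (clinical scores, neurophysiological measures) as within-subject factors". The tested effects follow: "The main effects of Time (pre, post) and Time X Group (unilateral vs bilateral TBS) interaction will be investigated". No baseline covariate is named. On missing data it says: "This analysis take into account missing data, avoiding the use of additional methods such as multiple imputations".

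Table 3 schedules more scores than these two. In the treatment phase HRSD-17 is taken at "Baseline, end of week 2 and 4 (and final week of additional treatment for non-remitters"). QIDS-SR16 and BAI are taken at the end of every treatment week. MADRS has no score between baseline and week 4.

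The primary analysis of HRSD-17 is different: "An ANCOVA will be performed with the baseline HRSD-17 as controlling (i.e., covariate) and the final HRSD-17 score as the dependent outcome variable", and "During ANCOVA, potential missing data will be addressed using multiple imputation methods".

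**The concern.** Two features of the secondary model cost something.

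- **Precision.** With two occasions and a free baseline mean in each arm, the interaction is the difference between arms in mean change. The primary analysis conditions on baseline for the same scale and the same arms. The secondary comparison therefore uses the weaker contrast without need.
- **Missing data.** A likelihood model protects only against dropout that is explained by data in the model. Here a participant who leaves before the post score contributes a baseline and nothing else, even if the week-2 or week-4 score was recorded. The model is then valid only if dropout depends on baseline and group alone. The design makes this doubtful. Under Study design and overview, only participants not in remission at week 4 go on to weeks 5 and 6, so the chance to drop out in those weeks depends on the week-4 score, which the model leaves out.

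At stake are the width of the intervals for the secondary arm comparisons and, if dropout differs between arms, a modest bias in them.

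**Working it through.** The protocol gives no SDs, correlations or sample size for this model, so there is no figure of its own to reproduce. All SDs and correlations below are assumptions. The 6–8% dropout is from the Sample size section.

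**1. Change score against baseline adjustment, complete data.** Let ρ be the baseline-final correlation and r the baseline SD divided by the final SD. In units of the final variance, per participant:

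- change score: 1 + r² − 2ρr
- baseline-adjusted: 1 − ρ²
- difference: (1 + r² − 2ρr) − (1 − ρ²) = (r − ρ)², which is never negative

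So the change score is never the more precise of the two. With r = 1 the ratio is 2(1 − ρ)/(1 − ρ²) = 2/(1 + ρ).

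| ρ | r | Change score | Adjusted | Ratio | Excess variance |
|---|---|---|---|---|---|
| 0.4 | 1.0 | 1.20 | 0.84 | 1.43 | 43% |
| 0.4 | 0.8 | 1.00 | 0.84 | 1.19 | 19% |
| 0.4 | 0.6 | 0.88 | 0.84 | 1.05 | 5% |
| 0.6 | 1.0 | 0.80 | 0.64 | 1.25 | 25% |
| 0.6 | 0.8 | 0.68 | 0.64 | 1.06 | 6% |
| 0.6 | 0.6 | 0.64 | 0.64 | 1.00 | 0% |

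A ratio r below 1 is plausible: Table 2 requires HRSD-17 of at least 15 at entry, which truncates baseline scores but not final ones.

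**2. What the interim scores add to precision.** This is the generalized least squares variance with equal SDs, ρ of 0.3 to 0.5, week-2/final correlation of 0.5 to 0.8, and half of the dropouts leaving before week 2. Adding week 2 to the pre/post model lowers the variance as follows:

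- complete data: 0%
- 6–8% dropout: 0.4 to 1.7% (for example 1.479 to 1.461 at 8% dropout, ρ = 0.3, week-2/final 0.7)
- 20% dropout: 1.6 to 4.7%

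At 6–8% dropout, baseline adjustment alone lowers it by about 23 to 34%. Nearly all of the gain in precision comes from the adjustment.

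**3. Bias in the arm contrast when dropout depends on the week-2 score.** Large-sample simulation with SD 6, baseline-final correlation 0.4, week-2/final correlation 0.7, dropout log-odds of 1 per SD of the week-2 score, and no true difference; simulation error is about 0.02.

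| Dropout by arm | Mechanism | Pre/post bias (points) |
|---|---|---|
| 6% v 6% | same | 0.01 |
| 8% v 8% | same | 0.02 |
| 6% v 8% | same | −0.07 |
| 4% v 12% | same | −0.23 |
| 10% v 20% | same | −0.28 |
| 6% v 6% | opposite | 0.37 |
| 8% v 8% | opposite | 0.47 |

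With week 2 in the model, the bias is within 0.03 of zero in every row. A second set (79 per arm, final SD 6.5, same week-2/final correlation) gave −0.10 at 6% v 8%, −0.31 at 4% v 12% and −0.56 at 5% v 20%. A stronger dependence of dropout on the week-2 score gives figures of this larger size. Opposite mechanisms combined with 10% v 20% dropout gave 0.89, but that stacks two unfavourable assumptions at rates well above the anticipated ones.

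**The case against.** The strongest reply is that little hangs on this model. It is explicitly secondary, and the Sample size section calls the tests other than the primary and regression analyses exploratory. The primary ANCOVA has both baseline adjustment and multiple imputation. The model is also a template for many outcomes, some with no interim score, and a separate analysis plan may give the full visit structure. All of this stands and limits the weight of the point. It does not remove it, because the article itself fixes two time levels and sets imputation aside for this model. The general undertaking under Data analysis to handle missing values by published procedures does not change that.

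Several stronger readings are tempting but not supported:

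- **That the unused interim scores would bring a large gain in precision.** They add under 2% to the planned model at 6–8% dropout. Their value is protection against bias.
- **That 43% or 25% is the loss.** These figures need equal baseline and final SDs, which the protocol does not give.
- **That patients are discharged for early non-response.** Non-responders are discharged only after the two additional weeks, when the final score is due. Earlier discharge is for non-adherence.
- **That a bias of 0.3 points or more is to be expected.** It needs dropout that differs between arms in rate or mechanism. Both arms receive active iTBS, and the sham cTBS imitates sound and sensation, so nothing in the protocol predicts this.
- **That the model cannot be fitted because outcomes are called factors.** The scores are the dependent variables and time is the within-subject factor. The next sentence makes the intended model clear, so this is a matter of wording.

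Two further limits hold. The near-zero bias once week 2 is included follows from simulating dropout from that score. And week 2 cannot help with participants who leave before it.

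**Conclusion.** The point holds as a minor-to-moderate improvement to a secondary analysis. The Time X Group test as written is unbiased under randomization with complete data, but never more precise than the adjusted contrast. Its excess variance runs from nothing to 43% across the assumed correlations (0.4 to 0.6) and SD ratios (0.6 to 1).

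The statement that the model takes missing data into account is true only if dropout depends on baseline and group alone. If dropout follows early response, the bias in the arm contrast is about 0.1 HRSD-17 point or less at the anticipated 6–8% with a common mechanism, and roughly 0.2 to 0.6 points under the assumed unequal rates or opposite mechanisms. A reader should not infer that the primary non-inferiority result is affected by this model.

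**What to change.** For each clinical scale, fit a separate mixed model with the score as dependent variable and visit as within-subject factor. Use all scheduled initial-phase scores, with group, visit and visit X group, and constrain the baseline means to be equal across arms. The constraint gives the baseline adjustment and keeps the within-arm time effect that the protocol wants to test; entering baseline as a covariate would remove the pre level.

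Report the group contrast at the end of the initial phase, defined for every participant as the final initial-phase score: week 4 for week-4 remitters, week 6 for the others. Earlier scores enter as interim visits. State how the week-4 interim level is coded for remitters, whose week-4 score is their final one.

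Scales without an interim score, such as MADRS before week 4, gain mainly from the baseline adjustment. Use the interim scores as auxiliary variables in the multiple imputation for the primary ANCOVA as well.

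The cost is revised analysis wording and slightly more analysis work. All the scores are already scheduled.

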##### Primary outcome measure

Response to treatment will be primarily defined as a ≥ 50% reduction in pre-treatment symptom severity as measured by the HRSD-17 score. Treatment remission will be defined as a HRSD-17 score ≤ 7. These definitions of treatment response and remission are based on recent literature assessing the effects of rTMS in individuals with depression [33, 37, 38, 91, 92].

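### Response and remission are compared between arms without adjusting for baseline HRSD-17: a valid choice that gives away some precision on remission (minor)

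*Protocol article*

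**What the plan says.** All places are in the protocol article.

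- **Primary outcome measure.** Response is a reduction of at least 50% from the participant's own pre-treatment HRSD-17. Remission is absolute: "Treatment remission will be defined as a HRSD-17 score" of 7 or less.
- **Effectiveness of TBS treatment.** The secondary analysis comes first: outcomes "will be investigated with generalized linear mixed models with treatment groups (unilateral vs bilateral TBS) as between-subjects factor", with Time (pre, post) and Time × Group effects. On missing data it adds: "This analysis take into account missing data, avoiding the use of additional methods such as multiple imputations". Then comes the analysis at issue: "The binominal outcomes will also be examined using Chi-Squared tests, and the difference in proportion rates between the groups will be reported".
- **Non-inferiority analysis.** The primary ANCOVA has final HRSD-17 as outcome and baseline HRSD-17 as covariate. "During ANCOVA, potential missing data will be addressed using multiple imputation methods".
- **Data analysis (opening).** Everyone is included as randomised, and "data will be analyzed regardless treatment adherence and drop-outs". Further, "missing values in the data set (due to participants missing appointments, drop-out/discharge), if present, will be appropriately managed during analysis", by cited procedures.
- **Predictors of treatment response.** Regressions on responder status are planned with neurobiological predictors. Baseline HRSD-17 is among the controlling variables, and treatment group may be entered.
- **Sample size.** 158 evaluable participants and 6–8% expected dropout. Tests other than the primary ANCOVA and the predictor regression are called exploratory.

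**The concern.** Response and remission are the results that clinicians will read first, and both are defined under the primary outcome heading. Their reported arm effect is a raw difference in proportions. For remission this leaves out a measured variable that bears on the outcome: a participant entering at 15 needs an 8-point fall to reach 7, and one entering at 28 needs a 21-point fall. The trial adjusts for this same variable in its primary analysis, so the secondary comparison is less precise than the collected data allow. At stake is the width of the confidence interval for the remission difference, and to a much smaller degree for the response difference. The validity of the test is not at stake.

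**Working it through.** **1. Is the raw difference really the reported arm effect?** The chi-squared sentence says *also*, so the mixed models might be thought to cover the binary outcomes. They cannot usefully do so as a pre/post model. Entry requires HRSD-17 ≥ 15, so nobody is in remission (≤ 7) at the pre assessment, and nobody can yet show a 50% fall from baseline. Every pre value is *no*, and a Time × Group model of the binary outcome is degenerate. The predictor regressions may include group and baseline HRSD-17, but they promise no treatment difference. The raw difference in proportions is therefore the only arm effect stated for response and remission.

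**2. Inputs for the size.** From the article: N = 158, 1:1 allocation, entry score ≥ 15, remission ≤ 7, response = final score ≤ half of baseline. Assumed, because the article gives no score distribution: baseline about 22, SD 4, truncated at 15; final mean 12, SD 6.5; baseline-final correlation 0.2, 0.4, 0.5 or 0.6. The article states no power or precision for the chi-squared comparison, so there is no figure of its own to reproduce.

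**3. Formulae.** Ratio = variance of the raw difference ÷ variance of the standardised difference from a logistic model with arm and baseline. Variance saved = 1 − 1/ratio. CI narrowing = 1 − 1/√ratio. Equivalent sample = 158 × ratio.

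**4. Remission.** Two separate sets of simulated trials on these assumptions:

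| Correlation | Ratio, set A | Variance saved | Ratio, set B | Variance saved |
|---|---|---|---|---|
| 0.2 | 1.009 | 0.9% | 1.02 | 2.0% |
| 0.4 | 1.076 | 7.1% | 1.08 | 7.4% |
| 0.5 | 1.157 | 13.6% | 1.12 | 10.7% |
| 0.6 | 1.222 | 18.2% | 1.19 | 16.0% |

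At the extremes of set A, the raw analysis would need 158 × 1.009 ≈ 159 or 158 × 1.222 ≈ 193 participants to match the adjusted analysis with 158. The CI narrows by 1 − 1/√1.009 = 0.4% to 1 − 1/√1.222 = 9.5%.

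**5. Response.** The ratios in set A are 0.996, 1.001, 1.025 and 1.067, so the variance saved runs from none to 1 − 1/1.067 = 6.3%. Set B gives about 0.99 to 1.06. The gain is small because response is already measured against the participant's own baseline.

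**6. Validity and power.** A further simulation used slightly different assumed scores (baseline mean 23, SD 4.5, at least 15; final mean 12.5, SD 7; N = 158; 1,500 runs). The type I error of the unadjusted chi-squared test was 0.04–0.065. Power for a 3-point shift, chi-squared against baseline-adjusted logistic:

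| Correlation | Remission | Response |
|---|---|---|
| 0.2 | 0.533 vs 0.527 | 0.584 vs 0.593 |
| 0.35 | 0.567 vs 0.593 | 0.617 vs 0.631 |
| 0.5 | 0.538 vs 0.585 | 0.643 vs 0.663 |

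The largest loss is 0.585 − 0.538 = 0.047, about 5 points.

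**The case against.** The strongest reply is that an unadjusted comparison of proportions is legitimate in a randomised trial, holds its level, and is secondary here. The non-inferiority conclusion rests on an ANCOVA that already adjusts for baseline and uses multiple imputation. All of that stands, and it is why the point is minor. It does not remove the point, because the covariate is already collected and adjusting for it is free.

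Two stronger readings are tempting, and the documents do not support them.

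**Completers only, hence biased rates.** A reader might infer that dropouts fall out of the chi-squared test, because imputation is named for the ANCOVA and "This analysis take into account missing data, avoiding the use of additional methods such as multiple imputations" stands just before the chi-squared sentence. That remark belongs to the mixed models described before it. The opening of the data analysis section keeps all participants as randomised and says that missing values will be managed. No section says that the tests use observed cases only, and the coding of a missing binary outcome is a detail that an article may leave to the SAP.

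The possible effect can be illustrated, but only on assumptions. With 50% response among completers and dropouts counted as non-responders, 8% loss turns 50% into 0.50 × 0.92 = 46% in each arm, and the arm difference stays at 0. A 4-point difference needs unequal loss, for example 4% against 12% (0.50 × 0.96 = 48% and 0.50 × 0.88 = 44%). The article gives only 6–8% overall. Nor would multiple imputation under missing at random set dropouts to non-response, so it would not reproduce these figures.

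**Baseline largely decides remission.** This goes too far. In the simulation of step 6, with correlations of 0.2 to 0.5, the AUC of baseline for remission was 0.60–0.74 and McFadden R² was 0.02–0.12. Baseline is related to remission but does not determine it.

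**Conclusion.** The point holds as a matter of efficiency. The reported arm comparison of response and remission is unadjusted, while a covariate related to remission is available and already used in the primary analysis. Over assumed correlations of 0.2 to 0.6, adjustment saves roughly 1–18% of the variance of the remission difference and about 0–6% for response. These figures rest on assumed score distributions that are not in the documents; at a correlation near 0.2 the gain is negligible even for remission. Neither an invalid test nor a biased comparison has been shown. Priority: minor.

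**What to change.** For response and for remission, report the difference in proportions with a 95% CI from a logistic model with arm and baseline HRSD-17, standardised over the trial sample. Keep the chi-squared test as an unadjusted check.

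Derive both outcomes from the imputed final HRSD-17 data sets already planned for the ANCOVA, and pool the standardised differences across imputations. This aligns the rates with the as-randomised rule and with the primary analysis; it is not the repair of a demonstrated bias.

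The cost is a sentence or two in the analysis plan and a few lines of code. No new data are needed.
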